### 5.3.3 Additional Assessments

In addition to the above endpoints, the following parameters will be collected at baseline and during follow-up visits (as detailed in the clinical data collection table) and analyzed for changes:

- Body weight and BMI.
- Waist circumference and waist-to-hip ratio.
- Office blood pressure.
- Changes in heart rate variability (24-hour Holter monitoring).
- Plasma catecholamine levels (including epinephrine and norepinephrine).
- Device performance evaluation (as assessed by the operator).

## 5.4 Study Flow

### 5.4.1 Study Flowchart

This feasibility clinical study of endovascular denervation for T2DM will recruit up to 30 subjects across a maximum of three centers in mainland China.

**Enrollment period:** approximately 3 months.

**Follow-up period:** 24 months.

All subjects will be screened according to inclusion and exclusion criteria and enrolled in a non-randomized manner.

Clinical follow-up visits will be conducted at the following time points:

Day 7 post-procedure or before discharge (whichever comes first), 30 days (±7 days), 3 months (±14 days), 6 months (±30 days), 12 months (±30 days), and 24 months (±30 days) post-procedure.

**Screening+Baseline^*^**

**Angiography**

**+**

**EDN**

**N = 10**

**Inform consent**

**Inclusion criteria**

**Washout^*^**

**Baseline Data**

**Follow-ups**

**Enrollment+Procedure**

**7 days**

**3 months**

**12 months**

**24 months**

**6 months**

**30 days**

**Figure 5-1 Study Flowchart**

* Subjects eligible for enrollment who are taking α-glucosidase inhibitors must undergo a 2-week washout period before being considered for enrollment.

Notes: A subject is considered to have completed the study if they have completed the 24-month follow-up, withdrawn (due to death or loss to follow-up), or exceeded the last follow-up window (i.e., >30 days beyond the scheduled visit window). For subjects who withdraw early, data collected up to the point of withdrawal will be retained and analyzed, but no further data will be collected thereafter.

All subjects must discontinue metformin on the day of CTA or DSA examination.

###

### 5.4.2 Data Collection

Please note:

- The time window for the 30-day follow-up is ±7 days.
- The time window for the 3-month follow-up is ±14 days.
- The time windows for the 6-, 12-, and 24-month follow-ups are ±30 days.
- The table below (Table 5-2) summarizes all procedures and assessments required by the study protocol throughout the trial.

**Table 5-2 Clinical Data Collection Schedule**

|  | | **Screening^a^** | **Baseline (≤14 days pre-procedure)** | **Baseline Procedure / Enrollment (Day 0)** | **Follow-ups** | | | | | |
| --- | --- | --- | --- | --- | --- | --- | --- | --- | --- | --- |
|  |  |  |  |  | **Post-op 7 days or discharge** | **Post-op 30 days^b^ (±7)** | **Post-op 3 months^b^ (±14)** | **Post-op 6 months^b^ (±30)** | **Post-op 12 months^b^ (±30)** | **Post-op 24 months^b^ (±30)** |
| **On-site visit** | | X | X | X |  | X | X | X | X | X |
| **Informed consent** | | X |  |  |  |  |  |  |  |  |
| **Demographics (age, sex, race, etc.)** | | X |  |  |  |  |  |  |  |  |
| **Medical history** | | X |  |  |  |  |  |  |  |  |
| **Inclusion / exclusion criteria** | | X | X | X |  |  |  |  |  |  |
| **Physical exam (weight, height, waist & hip circumference, office BP)** | | X |  |  |  | X | X | X | X | X |
| **Antidiabetic medication / insulin use** | | X | X | X | X | X | X | X | X | X |
| **Other treatments (CV meds, anticoagulants, antiplatelets)** | | X | X | X | X | X | X | X | X | X |
| **EQ-5D-5L questionnaire** | |  | X |  |  |  |  | X |  |  |
| **Lab tests** | **CBC** | X |  |  | X | X | X | X | X | X |
|  | **Pregnancy test (if applicable)** |  | X |  |  |  |  |  |  |  |
|  | **Renal function^c^** | X |  |  | X | X | X | X | X | X |
|  | **Coagulation profile** | X |  |  |  |  |  |  |  |  |
|  | **OGTT^d^** |  | X |  |  |  |  | X | X | X |
|  | **14-day CGM^e^** |  | X^q^ |  |  | X | X | X | X | X |
|  | **HbA1c** | X^o^ | X^p^ |  |  | X | X | X | X | X |
|  | **Fasting glucose** |  |  |  |  | X | X |  |  |  |
|  | **Fasting insulin** |  |  |  |  | X | X |  |  |  |
|  | **HOMA-β and HOMA-IR^f^** |  | X |  |  | X | X | X | X | X |
|  | **Lipid profile^g^** |  | X |  |  | X | X | X | X | X |
|  | **Liver function^h^** | X |  |  | X | X | X | X | X | X |
|  | **Catecholamines^i^** |  | X |  |  | X | X | X | X | X |
| **HRV (24-h Holter)^j^** | |  | X |  |  | X |  | X |  |  |
| **Radiographics** | **Celiac CTA^k^** | X |  |  |  |  |  | X |  |  |
|  | **Celiac angiography (DSA)^l^** |  |  | X |  |  |  | X |  |  |
| **EDN procedure/device info^m^** | |  |  | X |  |  |  |  |  |  |
| **AE/ADE/SAE/SADE assessment^n^** | |  |  | X | X | X | X | X | X | X |

Notes and Annotations

Remarks: If a subject does not meet the inclusion criteria during the screening period, re-screening may be conducted after investigator assessment.

Annotations:

a. Subjects taking α-glucosidase inhibitors during screening require a 2-week washout period before enrollment.

b. All follow-up visits are calculated from the date of the baseline procedure.

c. Renal function includes BUN, serum creatinine, and eGFR (calculated using CKD-EPI formula).

d. OGTT: 5-point sampling (0, 30, 60, 90, 120 minutes) with glucose, insulin, and C-peptide measurement; indices include Matsuda Index, insulin clearance, insulinogenic index, C-peptide index, late insulin response, and oral disposition index.

e. 14-day CGM for mean glucose, postprandial excursions, nocturnal excursions, and time-in-range (TIR).

f. β-cell function and insulin resistance assessed using HOMA-β and HOMA-IR. HOMA-β = 20 × FINS / (FBG – 3.5); HOMA-IR = (FBG × FINS) / 22.5. (FINS = fasting insulin μU/mL, FBG = fasting glucose mmol/L).

g. Lipid profile includes TG, TC, HDL-C, LDL-C.

h. Liver function tests include ALT, AST, ALP, TBil, GGT.

i. Catecholamines include norepinephrine and epinephrine.

j. HRV evaluated by 24-hour Holter monitoring.

k. Screening CTA of the celiac trunk excludes vascular abnormalities.

l. Pre-EDN angiography excludes vascular anomalies; at 6 months, DSA required if CTA suggests >50% stenosis; no DSA if CTA is normal.

m. Device and procedural information collected for device performance evaluation.

n. Includes major adverse events (MAE), major adverse cardiovascular and cerebrovascular events (3MACE), and hypo-/hyperglycemia.

o. HbA1c results within 1 month prior to screening are acceptable.

p. HbA1c results within 14 days prior to baseline procedure are acceptable; otherwise, repeat testing required.

q. Baseline CGM within 20 days prior to procedure is acceptable; follow-up CGM initiated at visit.

Laboratory tests in this trial include:

- CBC: WBC, RBC, LY, NEU, HCT, Hb, PLT

- Pregnancy test

- Renal function: BUN, SCr, eGFR

- Coagulation profile: PT, APTT, TT, FIB, INR

- Fasting glucose, fasting insulin, fasting C-peptide

- OGTT

- HbA1c

- Lipid profile: TC, HDL-C, LDL-C, TG

- Liver function: ALP, ALT, AST, TBil, GGT

- Catecholamines: norepinephrine, epinephrine

| **Test Item** | **Screening** | **Baseline (≤14 days pre-procedure)** | **Post-op 7 days or discharge** | **Post-op 1 month (±7 days)** | **Post-op 3 months (±14 days)** | **Post-op 6 months (±30 days)** | **Post-op 12 months (±30 days)** | **Post-op 24 months (±30 days)** |
| --- | --- | --- | --- | --- | --- | --- | --- | --- |
| CBC – 3 ml | X |  | X | X | X | X | X | X |
| HbA1c – 3 ml | X |  |  | X | X | X | X | X |
| Renal + Liver function – 5 ml | X |  | X |  | X | X | X | X |
| Coagulation – 3 ml | X |  |  |  |  |  |  |  |
| Pregnancy test – 5 ml |  | X |  |  |  |  |  |  |
| Lipid profile – 5 ml |  | X |  |  | X | X | X | X |
| OGTT + Insulin + C-peptide – 42.5 ml (3.5 ml for glucose each time point, 5 ml for insulin + C-peptide) |  | X |  |  |  | X | X | X |
| Fasting insulin – 5 ml |  |  |  | X | X |  |  |  |
| Fasting glucose – 3.5 ml |  |  |  | X | X |  |  |  |
| Catecholamines – 5 ml |  | X |  | X | X | X | X | X |

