**Table 5-1 Inclusion Criteria**

| **Clinical Inclusion Criteria** | 1. Age between 18 and 65 years (inclusive). 2. The subject understands the requirements of this clinical trial and the treatment, agrees to and is able to complete all required follow-up assessments, and has signed the informed consent form prior to any trial-related procedures or interventions. 3. Diagnosed with T2DM for 1–15 years (according to WHO diagnostic criteria). 4. On stable treatment for ≥3 months with metformin (≥1000 mg/day) in combination with 1–3 oral antidiabetic drugs (OADs) and/or insulin (any dose). Eligible OADs include: insulin secretagogues (sulfonylureas/meglitinides), thiazolidinediones (TZDs), and α-glucosidase inhibitors (see note). The combined OAD dose must be at least half of the maximum approved dose stated in the drug label. 5. Despite ≥3 months of OAD therapy, glycemic control remains inadequate, with HbA1c between 7.5% and 10.5% (as determined at baseline). 6. Body mass index (BMI) between 18 and 40 kg/m² (inclusive).   Note: Subjects receiving α-glucosidase inhibitors must undergo a 2-week washout period before enrollment. |
| --- | --- |

###

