#### 5.4.7.2 Concomitant Antidiabetic Therapy and Lifestyle Management

Subjects must be on stable OAD therapy for at least 3 months prior to the baseline procedure (subjects taking α-glucosidase inhibitors must undergo a 2-week washout before enrollment). After EDN, OADs and insulin regimens will be adjusted by the investigator according to blood glucose levels and guideline recommendations (see Sections 5.4.7.3 and 5.4.7.4). All changes in OADs and insulin type/dose must be documented at follow-up visits.

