#### 5.4.7.3 Principles for Rescue Treatment of Hyperglycemia

For subjects meeting any of the following hyperglycemia definitions, and where no definite cause can be identified, investigators may initiate insulin therapy on top of existing treatment as rescue therapy, based on clinical judgment.

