**Recommended principles of rescue treatment for hyperglycemia:**

- Initiate insulin therapy in addition to existing treatment, including intensifying basal insulin dose and/or adding short-acting or rapid-acting insulin.
- Adjust basal insulin dose every 3–5 days according to fasting blood glucose (FBG). Increase by 1–4 U per adjustment until target FBG is achieved. The maximum basal insulin dose should not exceed 0.5–0.6 U/kg/day.

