**Management principles:**

- If hypoglycemia occurs, immediately administer 15–20 g glucose and recheck blood glucose after 15 minutes.
- In subjects receiving insulin therapy, glycemic targets should be relaxed to strictly avoid recurrent hypoglycemia for several weeks, to partially reverse hypoglycemia unawareness and reduce future risk.
- Medication reduction should follow the sequence: Insulin (if applicable) → Sulfonylureas → Glinides → Thiazolidinediones → Metformin (final adjustment of metformin at investigator’s discretion).

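### In subjects using insulin, HOMA-IR and HOMA-β as defined move partly with injected insulin, so their change from baseline is not a clean measure of resistance or β-cell function

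*Protocol*

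**What the plan says.** Annotation f to the Clinical Data Collection Schedule (Table 5-2 in section 5.4.2) defines "HOMA-β = 20 × FINS / (FBG – 3.5); HOMA-IR = (FBG × FINS) / 22.5", with "FINS = fasting insulin μU/mL, FBG = fasting glucose mmol/L". Section 5.3.2 makes the change in both indices a secondary endpoint at 1, 3, 6, 12 and 24 months.

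Table 5-1 admits patients on metformin "in combination with 1–3 oral antidiabetic drugs (OADs) and/or insulin (any dose"). Insulin can then change after the procedure by three routes:

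- Section 5.4.7.2, general adjustment: "After EDN, OADs and insulin regimens will be adjusted by the investigator according to blood glucose levels and guideline recommendations".
- Section 5.4.7.3, rescue: "investigators may initiate insulin therapy on top of existing treatment as rescue therapy". The recommended principles there add: "Initiate insulin therapy in addition to existing treatment, including intensifying basal insulin dose and/or adding short-acting or rapid-acting insulin".
- Section 5.4.7.4, after hypoglycemia: "Medication reduction should follow the sequence: Insulin (if applicable") and then the oral drugs.

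Section 6.4 analyses the secondary endpoints in the ITT and PPS populations, pools the centers, and compares continuous outcomes before and after by paired t-test. There is no control group (section 5.4.3).

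C-peptide is collected. The blood-volume table lists "OGTT + Insulin + C-peptide – 42.5 ml" at baseline, 6, 12 and 24 months. Fasting C-peptide also appears in the laboratory list, but no draw is scheduled for it at 1 and 3 months, where only fasting glucose and fasting insulin are listed. Neither HOMA formula uses C-peptide. No rule separates insulin users from non-users for HOMA or takes account of the time since the last injection.

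**The concern.** An index built on measured fasting insulin describes the patient's own insulin only if the patient's own insulin is what is measured. In someone injecting insulin, FINS can also contain injected insulin, to a degree that depends on the preparation, the timing and the assay. Because the regimen may differ between baseline and follow-up, the within-patient difference tested in section 6.4 mixes a change in physiology with a change in treatment. With no control arm, there is no comparison in which the treatment part could cancel.

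Sections 3.3.2.2 and 3.3.2.6 present improved insulin resistance as the route by which EDN acts, so a fall in HOMA-IR is likely to be read as support for that mechanism. In insulin users the plan as written could not separate such a fall from a lower injected dose.

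**Working it through.** The protocol states no figure to reproduce here. The check evaluates its two formulas directly.

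**1. Sensitivity to an injected component.** Write FINS = E + X, with E endogenous insulin and X the injected contribution to the measured value. At fixed glucose and fixed E, removing X lowers both indices by the fraction X/(E + X). E, X and glucose below are assumptions, since the protocol gives none of them: glucose 9 mmol/L, E = 10 μU/mL.

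| X (μU/mL) | HOMA-IR = 9 × (10 + X)/22.5 | HOMA-β = 20 × (10 + X)/(9 − 3.5) |
|---|---|---|
| 0 | 4.0 | 36.4 |
| 5 | 6.0 | 54.5 |
| 10 | 8.0 | 72.7 |
| 20 | 12.0 | 109.1 |

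Going from X = 5 to X = 0 takes HOMA-IR from 6.0 to 4.0 and HOMA-β from 54.5 to 36.4. Each falls by 5/15 = 33%. HOMA-IR then looks better and HOMA-β worse, although resistance and secretion were held constant.

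**2. Dilution in the cohort mean.** Let a share s of subjects use insulin, with X halving from 10 to 5 and all else as above. Mean HOMA-IR goes from 8s + 4(1 − s) to 6s + 4(1 − s).

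| s | Before | After | Change |
|---|---|---|---|
| 10% | 4.4 | 4.2 | −4.5% |
| 30% | 5.2 | 4.6 | −11.5% |
| 50% | 6.0 | 5.0 | −16.7% |
| 70% | 6.8 | 5.4 | −20.6% |

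Mean HOMA-β changes by the same percentages. The protocol does not give s.

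**3. If glucose is not fixed.** Stopping insulin may raise glucose. Take X from 5 to 0, starting from HOMA-IR 6.0 and HOMA-β 54.5 at 9 mmol/L, and let follow-up glucose vary.

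| Follow-up glucose (mmol/L) | HOMA-IR = 10G/22.5 | HOMA-β = 200/(G − 3.5) |
|---|---|---|
| 9 | 4.0 (−33%) | 36.4 |
| 11 | 4.9 | 26.7 |
| 13.5 | 6.0 (0%) | 20.0 |
| 15 | 6.7 (+11%) | 17.4 |

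The net change in HOMA-IR can take either sign. HOMA-β falls throughout.

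**4. The earlier 11-patient study in section 3.2.** It reports HOMA-IR 13.3 falling to 6.0 and fasting glucose 227.2 falling to 181.8 mg/dL, together with lower insulin use. Assuming annotation f's formulas apply and dividing mg/dL by 18:

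- Glucose: 227.2/18 = 12.6 and 181.8/18 = 10.1 mmol/L (−20%).
- Implied FINS: 13.3 × 22.5/12.62 = 23.7 and 6.0 × 22.5/10.1 = 13.4 μU/mL (−44%).
- HOMA-IR had FINS stayed at 23.7: 10.1 × 23.7/22.5 = 10.6, against the reported 6.0.
- Implied HOMA-β: 20 × 23.7/(12.62 − 3.5) = 52, falling to 20 × 13.4/(10.1 − 3.5) = 41. The reported C-peptide AUC rose from 0.23 to 0.28.

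Most of that fall in HOMA-IR came through the insulin term, and implied HOMA-β moved opposite to C-peptide. This treats group values as one patient, so it is approximate.

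**The case against.** The best defence is that the protocol already holds most of what is needed. C-peptide is sampled with the OGTT, annotation d lists a C-peptide index, insulin use is recorded at every visit, and medication change is itself a secondary endpoint. How HOMA is split by insulin use could be left to an analysis plan that is not shown, and this is a feasibility trial without a formal hypothesis. All of this limits the importance of the point. It does not remove it: the formula, eligibility, insulin rules, analysis sets and test are fixed in the protocol, and an analysis plan cannot supply C-peptide at 1 and 3 months if it was never assayed.

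Four stronger readings are tempting and not supported.

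- A reader might infer that these endpoints follow injected dose instead of physiology. Insulin is optional under Table 5-1, the share of users is not given, and in users the measured value can mix both sources.
- A reader might infer that insulin is the first drug withdrawn after EDN in general. The insulin-first order in section 5.4.7.4 applies to hypoglycemia; section 5.4.7.2 sets no order.
- A reader might infer a bias in favor of the device. A dose cut makes HOMA-IR look better and HOMA-β worse; rescue does the reverse. Step 3 shows that even the sign for HOMA-IR is open once glucose moves.
- A reader might take the earlier study as proof of artefact. A true fall in resistance would also lower fasting insulin. Those figures show only that the two explanations cannot be separated.

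**Conclusion.** The point holds for subjects on insulin at baseline or follow-up, including those given rescue insulin. In them HOMA-IR and HOMA-β move partly with injected insulin, and no provision in the protocol corrects this. The size depends on the share of users, insulin type, injection timing and assay, none of which is stated. The 33% change in each index, and the 4.5% to 20.6% change in the cohort mean, rest on assumed insulin values and on fixed glucose and endogenous insulin; they are illustrations, not estimates.

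HOMA in subjects never on insulin is not affected in this way, and neither primary endpoint depends on it. This is a weakness in a secondary endpoint that should be put right because the remedy is cheap.

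**What to change.** In annotation f and section 6.4:

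1. For all subjects at baseline, 6, 12 and 24 months, make the main analysis of β-cell function and insulin resistance a named fasting measure computed from the 0-minute OGTT glucose and C-peptide, with its formula written out. This removes the direct contribution of injected insulin. It does not remove any effect of treatment on glucose or on secretion, and the report should say so.
2. Report FINS-based HOMA, and the insulin-based OGTT indices in annotation d, separately by insulin use from the records already kept. Label the result in subjects off insulin at both visits as supportive: that subset is selected after baseline and drops those who needed rescue insulin.
3. At 1 and 3 months, either run fasting C-peptide on the tube already drawn, or report HOMA only for subjects not using insulin and label it descriptive. The blood-volume table allots 5 ml for fasting insulin at these visits, the same volume it allots to insulin plus C-peptide at each OGTT point (5 × (3.5 + 5) = 42.5 ml).

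When making the change, align the visit lists in sections 5.4.13 and 5.4.14, which do not name the OGTT, with the schedule, which requires it at 12 and 24 months.

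The cost is wording, smaller numbers for FINS-based HOMA, and possibly one added assay at two visits.

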### 5.4.3 Treatment Assignment

After signing the informed consent form (ICF) approved by the ethics committee, and meeting all inclusion criteria while not meeting any clinical exclusion criteria, subjects will be considered for enrollment. Subjects receiving α-glucosidase inhibitors must undergo a 2-week washout period before enrollment.

This clinical trial has no control group. All eligible subjects will undergo baseline angiography during the procedure. If no angiographic exclusion criteria are met, they will receive EDN treatment using the endovascular denervation system developed by Shanghai Brattea Medical Technology Co., Ltd. The enrollment time point is defined as the insertion of the EDN catheter into the guiding sheath.

### 5.4.4 Subject Screening

Before any trial-specific screening procedures, eligible subjects for EDN will receive a detailed explanation of the study from the investigator, and will be required to sign the ICF. After signing, the subject will be assigned a screening number and recorded in the screening log.

If a subject does not meet inclusion criteria during screening, re-screening may be conducted at the investigator’s discretion. Investigators must maintain complete screening records for all subjects, including both those deemed eligible and those who failed screening.

### 5.4.5 Informed Consent

Prior to any study-specific assessments or procedures, subjects who meet the clinical inclusion criteria must sign the ICF approved by the ethics committee.

Investigators must allow sufficient time for subjects to review the ICF and address any questions raised. Even if a subject signs the ICF, study staff must explain that the final eligibility will be determined by angiographic findings, which may exclude the subject from participation.

### 5.4.6 Screening Period

Only after signing the ICF may a subject undergo screening. Screening is intended to confirm whether the subject meets inclusion and exclusion criteria.

The screening process includes review of the subject’s medical history and diagnostic records, as well as collection of the following information (unless otherwise specified):

- Confirmation of compliance with inclusion criteria and absence of exclusion criteria.
- Demographic data: age, sex, ethnicity (per local regulatory requirements).
- Physical examination: height, weight, waist and hip circumference, office blood pressure.
- Medical history: duration of diabetes, complications, comorbidities, surgical history.
- Antidiabetic medication and insulin use.
- Concomitant treatments (e.g., cardiovascular drugs, anticoagulants, antiplatelets).
- Laboratory tests:
- Complete blood count (CBC).
- Coagulation profile.
- Renal function: BUN, serum creatinine, eGFR.
- Liver function: ALT, AST, ALP, total bilirubin, GGT.
- HbA1c.
- Celiac CTA.*

*CTA results within 30 days prior to baseline procedure are acceptable. Metformin must be withheld on the day of CTA.

**Washout Period**

Subjects who meet clinical screening criteria but are taking α-glucosidase inhibitors must discontinue them for 2 weeks prior to enrollment. During this washout period, all other antidiabetic medications must remain unchanged. Subjects requiring a washout must complete this period before entering the baseline phase.

### 5.4.7 Baseline Period (within 14 days pre-procedure)

For subjects who pass screening, the following data must be collected within 14 days prior to the baseline procedure:

- Antidiabetic medication and insulin use.
- Concomitant treatments (cardiovascular, anticoagulant, and antiplatelet therapies).
- Laboratory assessments:
- Glucose metabolism: 5-point OGTT, 14-day CGM (may start up to 16 days before procedure, but duration must be ≥14 days), and HbA1c.
- β-cell function and insulin resistance: 5-point insulin and C-peptide test, HOMA-IR, HOMA-β.
- Lipid profile: triglycerides, total cholesterol, HDL-C, LDL-C.
- Plasma catecholamines: norepinephrine and epinephrine.
- Pregnancy test (serum) for women of childbearing potential within 7 days pre-procedure.
- Heart rate variability: 24-hour Holter monitoring.
- Quality of life/lifestyle assessment: EQ-5D-5L questionnaire.
- Reconfirmation of inclusion and exclusion criteria.

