**Table 5-2 Exclusion Criteria**

| **Clinical Exclusion Criteria** | I. Subjects with any of the following medical history or conditions:  1.Type 1 diabetes mellitus, latent autoimmune diabetes in adults (LADA), or any form of secondary diabetes.  2.History of aortic disease (e.g., aneurysm or dissection) or aortic surgery (including prior celiac denervation).  3.Baseline CTA showing aortic aneurysm/dissection, abnormal hepatic artery anatomy, or other vascular abnormalities unsuitable for ablation (e.g., severe tortuosity or stenosis, intraluminal thrombus, unstable plaques, as judged by the investigator).  4.≥2 self-reported or documented episodes of severe hypoglycemia within the past 6 months (defined as hypoglycemia with severe cognitive impairment requiring assistance).  5.≥1 documented episode of hyperglycemic crisis within the past 6 months requiring hospitalization (including diabetic ketoacidosis or hyperosmolar coma).  6.Severe diabetic complications considered unsuitable for enrollment by the investigator (e.g., advanced retinopathy, nephropathy, vasculopathy, neuropathy, or diabetic foot).  7.Major adverse cardiovascular or cerebrovascular event (MACCE) within the past 6 months, including cerebrovascular accident (CVA), transient ischemic attack (TIA), heart failure (NYHA class III–IV), acute myocardial infarction, or unstable angina requiring hospitalization (including history of CABG or coronary stent implantation), as well as uncontrolled or severe arrhythmias.  8.Severe autonomic neuropathy (e.g., orthostatic hypotension, gastroparesis).  9.Uncontrolled severe hypertension (SBP ≥160 mmHg or DBP ≥100 mmHg) or hypotension (BP <90/50 mmHg).  10.Renal insufficiency or history of renal failure with baseline estimated glomerular filtration rate (eGFR) <60 mL/min/1.73 m².  11.Chronic active hepatitis, severe hepatobiliary disease (including cirrhosis), or hepatic insufficiency (ALT and/or AST >3× ULN, or total bilirubin >2× ULN).  12.Acute or chronic pancreatitis during screening or baseline period.  13.Acute systemic infection during screening or baseline period.  14.History of bleeding tendency or coagulopathy (PT, APTT, or INR >2× ULN; platelet count <80×10⁹/L or ≥700×10⁹/L).  15.Active peptic ulcer disease or gastrointestinal bleeding within the past 3 months.  16.Symptomatic cholelithiasis (including gallbladder, extrahepatic bile duct, or intrahepatic bile duct stones) without effective treatment (e.g., cholecystectomy, bile duct stone removal, internal/external drainage).  17.Other endocrine or metabolic disorders, including hyperthyroidism, hypothyroidism, acromegaly, or Cushing’s syndrome.  18.Autoimmune disease.  19.Active or high-risk malignancy, or life expectancy <12 months.  20.Major surgery within the past 3 months.  21.Hemoglobinopathies or hemolytic anemia that may interfere with evaluation of primary endpoints.  22.Psychiatric disorders that preclude compliance with study procedures.  Note: Subjects not meeting inclusion criteria during screening may be rescreened if deemed appropriate by the investigator.  II. Subjects with prior or expected use of the following medications or treatments: 23. GLP-1 receptor agonists, DPP-4 inhibitors, or SGLT-2 inhibitors within 3 months prior to screening. 24. Systemic or intra-articular corticosteroid therapy within 3 months prior to screening (excluding topical, inhaled, or ophthalmic use). 25. Use of weight-loss drugs (e.g., orlistat) or other weight-reducing interventions (e.g., herbal medications, acupuncture, diet therapies) within 3 months prior to screening. 26. History or expectation of undergoing bariatric surgery (e.g., gastrectomy, liposuction). 27. Use of centrally acting sympatholytics or anticonvulsants within 3 months prior to screening or expected during the study. 28. Subjects requiring long-term anticoagulation who cannot undergo perioperative heparin bridging.  III. Subjects with the following conditions: 29. Body weight fluctuation >10% within the past 3 months. 30. Allergy or contraindication to contrast agents that cannot be adequately managed with premedication. 31. Known allergy to the investigational device or trial-related medications. 32. Participation in another clinical study within 3 months prior to enrollment. 33. Planned participation in another drug or device clinical trial within 24 months post-baseline procedure. 34. Pregnant or lactating women, or women planning pregnancy within 2 years (all women of childbearing potential must undergo a pregnancy test within 7 days prior to the baseline procedure). 35. Anticipated major changes in diet or exercise habits during the study period (e.g., due to religious practices, occupational reasons, or weight-loss programs). 36. Irregular day-night schedule (e.g., shift workers). 37. History of alcohol abuse, drug abuse, or substance dependence. 38. Severe blood loss or planned regular transfusion of blood products within 3 months prior to enrollment or during the study. 39. Any other condition judged by the investigator to pose risk to subject safety or significantly interfere with study outcomes. |

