### 5.4.12 6-Month Follow-up (±30 days)

At 6 months post-procedure, subjects must return for follow-up including:

- Physical exam (height, weight, waist & hip circumference, office BP).
- Antidiabetic medication/insulin use.
- Other treatments (cardiovascular, anticoagulant, antiplatelet therapies).
- Laboratory tests: CBC, renal function (BUN, creatinine, eGFR), fasting glucose & insulin, 14-day CGM, HbA1c, HOMA-IR & HOMA-β, lipid profile, liver function (ALT, AST, ALP, TBil, GGT), plasma catecholamines.
- HRV: 24-hour Holter monitoring.
- AE assessment and management (AE, SAE, SADE, UADE, USADE, ADE).
- OGTT (5-point)
- 14-day CGM.
- Insulin and C-peptide secretion tests (5-point), HOMA-IR, HOMA-β.
- CTA and/or DSA to assess vascular patency.
- EQ-5D-5L quality of life questionnaire.

Note: Subjects with CTA showing >50% stenosis at EDN sites must undergo DSA. If CTA is normal, DSA is not required. Metformin must be withheld on the day of CTA or DSA.

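### The only scheduled pregnancy test comes after a screening CTA done for the trial, and none is scheduled before the 6-month CTA or a DSA that it triggers

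*Protocol*

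**What the plan says.** **Pregnancy test.** Section 5.4.7 lists, for the baseline period, "Pregnancy test (serum) for women of childbearing potential within 7 days pre-procedure". Exclusion criterion 34 in the exclusion-criteria table of section 5.2.2 sets the same window: "all women of childbearing potential must undergo a pregnancy test within 7 days prior to the baseline procedure". In the Clinical Data Collection Schedule (section 5.4.2) the row "Pregnancy test (if applicable") has its only mark under Baseline. In the blood-sampling table that follows the schedule's notes, the row "Pregnancy test – 5 ml" likewise has its only mark under Baseline.

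**Imaging.** The same schedule marks celiac CTA at screening and at 6 months. Section 5.4.6 lists it among the screening assessments done after consent, and adds "CTA results within 30 days prior to baseline procedure are acceptable". The 6-month visit list in section 5.4.12 includes "CTA and/or DSA to assess vascular patency", and note l to the schedule reads "at 6 months, DSA required if CTA suggests >50% stenosis; no DSA if CTA is normal".

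**Related safeguards.** Criterion 34 excludes women who are pregnant, breastfeeding or intending pregnancy in the next two years. Section 5.4.6 asks at screening for "Confirmation of compliance with inclusion criteria and absence of exclusion criteria". Section 3.4.3 lists pregnancy, current or planned, as a contraindication to the device. Section 5.2.3.2 gives pregnancy as an example of a reason for which the investigator may withdraw a subject.

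**The concern.** The test is timed to protect against the day-0 angiography and ablation, and it does that. It does not cover the other abdominal contrast imaging that the protocol requires.

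At screening the order works against the participant. The CTA helps decide whether she passes screening, and the test is reserved for those who have passed. A woman with an unrecognised pregnancy would be scanned for the trial first and excluded afterwards. At 6 months every participant is due a CTA, and the last scheduled test was done before the procedure.

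What is at stake is participant safety: fetal exposure to radiation and contrast, for a trial purpose, that a simple test could have prevented. The HbA1c endpoint, the 30-day safety endpoint and the analyses are not affected.

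**Working it through.** The protocol states no figure for this point, so there is none to reproduce. The check sets the rows side by side and then works out the intervals.

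**1. Where test and imaging fall**

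| Visit | Pregnancy test | CTA / DSA |
|---|---|---|
| Screening | none | CTA (a result up to 30 days before EDN is accepted) |
| Baseline | yes, within 7 days before EDN | none |
| Day 0 | none (covered by the baseline test) | DSA before and after ablation |
| 6 months (± 30 days) | none | CTA; DSA if stenosis exceeds 50% |

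The visit lists in sections 5.4.6 and 5.4.12 agree with the tables: neither contains a pregnancy test.

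**2. Order at screening.** Section 5.4.7 collects baseline data from subjects who have passed screening, and section 5.4.6 places the CTA in screening. A CTA performed for the trial therefore precedes the only test.

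**3. Interval from screening CTA to test.** Inputs: CTA no earlier than day −30 (section 5.4.6); test between day −7 and day 0 (section 5.4.7).

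- CTA at day −30, test at day −7: 30 − 7 = 23 days.
- CTA at day −30, test at day 0: 30 − 0 = 30 days.
- The protocol sets no minimum gap. As an assumption, suppose the CTA is complete before a 14-day CGM that runs up to the procedure. The CTA is then at day −14 or earlier, and the shortest gap is 14 − 7 = 7 days. Without that assumption only the order and the 30-day maximum are supported.

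**4. Age of the last test at the 6-month CTA.** Inputs: visit window ± 30 days (section 5.4.2); 6 months taken as 180 days (assumption).

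- Window after EDN: 180 − 30 = 150 to 180 + 30 = 210 days.
- The test was done 0 to 7 days before EDN, so its age is 150 + 0 = 150 to 210 + 7 = 217 days.
- Taking 6 months as 183 days gives 153 to 220 days.
- A triggered DSA comes later still, by an interval the protocol does not fix.

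**5. Burden of an added test.** Inputs: volumes in the blood-sampling table.

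- Screening: CBC 3 + HbA1c 3 + renal and liver 5 + coagulation 3 = 14 ml.
- 6 months: CBC 3 + HbA1c 3 + renal and liver 5 + lipids 5 + OGTT set 42.5 + catecholamines 5 = 63.5 ml.
- One pregnancy test adds 5 ml: 14 + 5 = 19 ml and 63.5 + 5 = 68.5 ml.

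**The case against.** The strongest reply is that nothing here is contradictory. The protocol fixes one test, consistently, before its most invasive exposure, and surrounds it with other protections: the exclusion of current and planned pregnancy, review of the exclusion criteria at screening, baseline and procedure, the device contraindication, and the option to withdraw. On that view only an unplanned or unrecognised pregnancy slips through, and the 6-month gap is the weaker half, because the pregnancy would have to be still unrecognised at an on-site visit. Radiology departments may also test as routine, and the consent form, which was not available, may give instructions on pregnancy.

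Much of this stands. The documents do not conflict, the residual risk is an unrecognised pregnancy, and the screening CTA is the stronger case. But none of these protections detects such a pregnancy before the scan. The exclusion of planned pregnancy addresses intention, withdrawal is discretionary and acts only once the pregnancy is known, and the screening review has no test behind it. Before EDN the protocol does not rely on history alone; it requires a serum test. Nor does it leave all imaging-day precautions to local practice: sections 5.4.6 and 5.4.12 instruct sites to withhold metformin on the day of the scan and say nothing about pregnancy.

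The objection also rightly limits the numbers. The 7-day lower bound rests on an assumption about CGM timing, since note q to the schedule accepts a baseline CGM from up to 20 days before the procedure. The intervals are times between test and scan and do not measure risk.

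**Conclusion.** The concern holds. The schedule provides no pregnancy test before a screening CTA performed for the trial, nor before the 6-month CTA or a DSA that it triggers. At the day −30 limit the test follows the screening CTA by 23 to 30 days. At 6 months it is 150 to 217 days old when the CTA is done, taking 6 months as 180 days.

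The point is limited in three ways. It concerns only women of childbearing potential, whose number the protocol does not give (ages 18 to 65 are eligible). It does not apply where an existing routine CTA within the 30-day limit is accepted. It leaves every endpoint and analysis as it is. It is a safety correction the sponsor should make, and the conclusion does not depend on the 7-day lower bound or on how 6 months is converted to days.

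**What to change.** Keep the serum test within 7 days before EDN. For women of childbearing potential, add a pregnancy test whose result is known:

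- before any celiac CTA performed for the trial at screening;
- before the 6-month CTA, and before any DSA that follows it.

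The clinical team should set the type of test and the longest acceptable interval between test and scan, including whether a DSA done some time after the CTA needs a fresh test.

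Four places need editing: the pregnancy-test row of the Clinical Data Collection Schedule, the same row of the blood-sampling table, the assessment list in section 5.4.6 and the visit list in section 5.4.12. The notes there on withholding metformin are a natural place for the instruction.

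The cost is schedule wording and one or two additional routine tests per woman concerned. Each takes 5 ml if done on blood and can be added to draws already planned at those visits, provided the draw comes before the scan and the result is back in time. No extra visit is needed, and a test before the screening CTA would also avoid a scan in a woman who would then be excluded.
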